### Statistical Analysis

Statistical analyses will be performed using Stata^®^ (67) and the Statistical Package for the Social Sciences—SPSS^®^ (68). The overall significance level for this study will be 0.05 using two-tailed tests. The study results will be analyzed for two patient populations: the intention-to-treat (ITT(and the per-protocol (PP) analysis set. The ITT set will include all subjects who met the study eligibility criteria and received at least one week active/sham TBS treatment. The PP population thus will include all subjects from the ITT set who receive the protocol-specified treatment and complete the 6-week treatment regimen or withdrew before completion per the study protocol. Comparisons of baseline demographic and clinical characteristics and safety assessments will be performed on the ITT analysis set. The primary efficacy analysis will be performed using the PP analysis set.

Comparisons of baseline demographic and clinical characteristics between the study groups will be performed to ensure that the groups are balanced at baseline and that the randomization is successful. For comparison of means (continuous variables), the two-sample t-test or a nonparametric equivalent will be used. For comparison of proportions (categorical variables), the chi-square test or Fisher's exact test will be used, as appropriate. The change in MADRS total score from baseline to week 3 (primary endpoint) will be compared between the treatment groups using a linear mixed model (69) with a continuous dependent variable (MADRS score) to measure the primary outcome. For primary outcome subject will be the random effect and the fixed factors will be intervention (sham × active). Secondary outcomes will also follow the same pattern and the scales' scores will be the random effect and the fixed factors will be intervention (sham × active). Since patients will be taking different medications and dosages, the defined daily dose (DDD) will be used in the statistical analysis. This enables the inclusion of several medications and doses in the model, as medication groups (e.g., antidepressants, anticonvulsants, etc.).

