Clinical assessments will be conducted weekly until the end of week 3 and thereafter a final assessment will be conducted at the end of week 6. Adverse events will be evaluated every day during the first week and then once a week until the end of the week 6. The neuropsychological assessment battery will be applied before the patient is stimulated and at the end of the week 6 of intervention (**Table 2**).

**Table 2 T2:** Measurement outcomes over time.

Scales	Baseline	End of week 1	End of week 2	End of week 3	End of week 6
SCID I/P modified	X				
MADRS	X	X	X	X	X
YMRS	X	X	X	X	X
*WHOQOL-bref*	X	X	X	X	X
BIS-11	X	X	X	X	X
CGI-S	X	X	X	X	X
GAF	X	X	X	X	X
HAM-A	X	X	X	X	X
BRIAN	X	X	X	X	X
Morningness–Eveningness Questionnaire	X				
TMS' Typical side Effects Scale	X	X	X	X	X
UKU-SERS	X	X	X	X	X
Neuropsychological Assessment	X				X

SCID, Structured Clinical Interview; MADRS, Montgomery–Åsberg Depression Scale; YMRS, Young Mania Rating Scale; WHOQOL, World Health Organization questionnaire; BIS-11, Barratt Impulsivity Scale; GAF, Global Assessment of Functioning; HAM-A, Hamilton Anxiety Scale; BRIAN, Biological Rhythm Interview of Assessment in Neuropsychiatry; TMS, transcranial magnetic stimulation; UKU-SERS, Udvalg for Kliniske Undersøgelser Side Effect Rating Scale; CGI-S, Clinical global impression - Severity.

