### Intervention

TBS sessions will be performed using MagPro X100 TMS device (Magventure, Lucernemarken, Denmark) and Cool-B65 A/P (Magventure, Lucernemarken, Denmark) coil. An identical butterfly coil for both active and sham stimulation will be used. The coil will be positioned over the DLPFC and the cortical location will be obtained through anatomical measurements (F3 and F4 positions determined by the 10–20 Electroencephalographic International System) on the right and left. As most mixed depressive episodes are resistant to drug treatment and there are no clinical trials evaluating TBS specifically in mixed depressive episodes so far, we replied a study protocol (41) that evaluated TBS in resistant major depressive episodes of MDD. The bilateral TBS sections will be applied in the following order: first inhibitory stimulation—cTBS—in the right DLPFC followed by excitatory stimulation—iTBS—in the left DLPFC with the following parameters: in cTBS bursts of three pulses at 50 Hz (20-ms interval between stimuli) will be applied continuously for 120 s totaling 1800 pulses in the right DLPFC and iTBS bursts of three pulses at 50 Hz (20-ms interval between stimuli) will be applied for 2-s duration repeated every 10 s for a total time of 570 s also totaling 1800 pulses in the left DLPFC, both with 80% of visual motor threshold (64). We will use a magnetic stimulator device (MagVenture^©^, United States) in study mode for double-blind trials. Participants will perform one session a day over five consecutive days (Monday to Friday) at the first, second and third weeks and then sessions 2 days a week, with an interval of at least 1 day between sessions, for a further 3 weeks of active or sham TBS.

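### The set labelled ITT, which is the only set used for safety, requires a week of treatment, so patients stopped for harm during week 1 fall outside every stated analysis

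*Protocol article*

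**What the plan says.** All the rules on analysis sets stand in the Statistical Analysis section of the protocol article.

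- Number of sets: "The study results will be analyzed for two patient populations", namely ITT and per-protocol (PP). No safety set or all-treated set is named.
- ITT: "The ITT set will include all subjects who met the study eligibility criteria and received at least one week active/sham TBS treatment".
- Use of ITT: "Comparisons of baseline demographic and clinical characteristics and safety assessments will be performed on the ITT analysis set". The baseline comparison is meant to confirm balance and a successful randomisation.
- PP: "The PP population thus will include all subjects from the ITT set who receive the protocol-specified treatment". A further clause admits those who completed six weeks or withdrew in line with the protocol.
- Use of PP: "The primary efficacy analysis will be performed using the PP analysis set".

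Three other places bear on this. The Intervention section fixes a treatment week: "Participants will perform one session a day over five consecutive days (Monday to Friday) at the first, second and third weeks". The assessment paragraph that closes Inclusion and Exclusion Criteria sets the safety monitoring: "Adverse events will be evaluated every day during the first week", and weekly after that. Reasons for Withdrawal or Termination lists serious adverse effects, among them seizures and several kinds of severe pain, as grounds for withdrawal, judged case by case. The Introduction makes safety part of the main objective, together with efficacy.

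**The concern.** A safety population should hold everyone exposed to the intervention. Here entry depends on having tolerated the intervention for a week, and failure to tolerate it is one of the things that safety analysis is meant to measure. The patients most informative about early harm are therefore the ones that the rule removes, and they leave both the numerator and the denominator. The protocol monitors adverse events most closely in the same week whose treatment stoppers it then excludes.

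The label is a second problem. Intention-to-treat means that membership is settled at randomisation. A set defined by later exposure is a post-randomisation subset. A baseline table drawn from it describes those who stayed for a week, and it cannot show whether randomisation worked.

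At stake is the credibility of the safety result in a trial that describes itself as the first in its field.

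**Working it through.** No figure in the protocol has to be reproduced here, because the point rests on set definitions. The check is one of logic, followed by an illustration of size.

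**Step 1: who is in which set**

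1. Safety set = ITT set.
2. ITT requires at least one week of active or sham stimulation.
3. One week in weeks 1 to 3 = 5 sessions. A patient who stops after session 1, 2, 3 or 4 has not received a week and is not in ITT.
4. PP is a subset of ITT, so the same patient is not in PP. The PP clause on protocol-conform withdrawal does not bring the patient back, because it applies only to members of ITT.
5. No third set exists. The patient is in no stated safety, baseline or efficacy analysis.

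**Step 2: the limits of the window**

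Sessions in total: 5 × 3 + 2 × 3 = 21. The window is a stop after sessions 1 to 4, that is 4/21 = 19% of the sessions. This share describes the schedule; it does not say how many patients are lost. A patient who stops after session 5, or who is withdrawn at the end of week 1 because a symptom scale has worsened, has received a week and stays in ITT. A patient with a week-1 event who continues treatment is also counted in full.

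**Step 3: size, under an assumption**

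Input from Sample Size Calculation: 45 patients per group. Assumption: k patients in one arm stop for harm before completing week 1, all 45 received some stimulation, and nobody else in the arm is excluded. The protocol gives no value for k, so a range is shown.

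- Rate among all treated = k/45
- Rate in the stated set = 0/(45 − k)

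| k | All treated | Stated ITT set |
|---|---|---|
| 0 | 0/45 = 0% | 0/45 = 0% |
| 1 | 1/45 = 2.2% | 0/44 = 0% |
| 2 | 2/45 = 4.4% | 0/43 = 0% |
| 3 | 3/45 = 6.7% | 0/42 = 0% |
| 4 | 4/45 = 8.9% | 0/41 = 0% |
| 5 | 5/45 = 11.1% | 0/40 = 0% |

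For scale, the protocol recruits 90 to retain 82, an allowance of 90 − 82 = 8 losses over both arms, for any cause and over six weeks. A k of 5 in one arm lies within that allowance, but nothing in the protocol says that it is likely.

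**The case against.** **The events are not lost.** Adverse events are evaluated daily in week 1, and nothing says that a serious event would go unrecorded or unreported. This stands as far as collection goes. The loss is at the analysis: "safety assessments will be performed on the ITT analysis set", and these patients are not in that set.

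**Few patients may be affected.** Measurement of Variables and Outcomes calls serious events such as seizures very rare and lists mild complaints as the commonest, and withdrawal for harm is a case-by-case judgement. This stands too. The number could be zero, and then nothing changes. The rule is still wrong in advance, because it does damage in exactly the cases where early harm occurs.

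**Analysis sets belong in the analysis plan, or this is an ordinary modified ITT.** Neither holds. The article does not leave the sets open: it defines them and assigns safety to one of them. The set is called plain ITT. A wish for a first post-baseline MADRS score, due at the end of week 1, might explain a minimum exposure for efficacy. It gives no reason for one in safety, where observation starts on day 1.

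**Readings that go too far.** A reader might infer that the rule makes active stimulation look safer than sham. That would need more harm-related week-1 stops on active than on sham, and the protocol has no data on this; the rule applies to both arms. A reader might also infer that early intolerance is the commonest harm of the device. The protocol lists side effects but gives no timing for them. Finally, one might read this point as deciding that primary efficacy should move from PP to ITT. Redefining ITT does not by itself change the primary analysis set, and that choice needs its own argument.

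**Conclusion.** The point holds for the safety set and for the ITT label. By the protocol's own definitions, a patient who stops before completing the five sessions of week 1, including one withdrawn for a serious adverse effect, is left out of the planned safety analysis and of every other stated analysis. Harm is under-reported in whichever arm such stops occur.

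The size is unknown. With 0 to 5 harm-related week-1 stops among 45 in one arm, a true rate of 0% to 11.1% would appear as 0%. That range is an assumption. The conclusion about the sets does not depend on it; it rests only on reading a week of treatment as the five sessions scheduled for it. The effect on the baseline table is smaller and cannot be quantified from the protocol.

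Because safety is part of the main objective and the excluded events could be the most serious ones, the safety set must be corrected before the data are analysed.

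**What to change.** Replace the set definitions in Statistical Analysis:

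- **Safety set:** every patient who received any active or sham stimulation, however little, analysed as treated. Use it for all summaries of adverse events and of discontinuation.
- **ITT set:** every randomised patient, analysed as randomised, with no minimum exposure. Use it for the baseline tables and for the analyses described as ITT efficacy.

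The change to the text is about two sentences. It has two costs. Reported adverse-event rates may become slightly less favourable. In addition, the protocol's Table 2 schedules the side-effect scale, the UKU-SERS and the MADRS at baseline and at the ends of weeks 1, 2, 3 and 6, and the article describes no assessment at withdrawal. Patients who stop in week 1 may therefore have no post-baseline scale scores. Their safety data would come mainly from the daily adverse-event evaluations, and in an ITT efficacy analysis they might contribute only a baseline MADRS. The report should state how many such patients there are in each arm and why they stopped.

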### Study Hypothesis

The main hypothesis of this study is that the active TBS on the right and left DLPFC in patients with mixed depression can produce a greater and statistically significant reduction in the primary outcome scale (MADRS) compared to sham TBS. Other aims of the study will be evaluate: TBS safety and tolerability; socio-demographic and clinical profiles; impact of DSM-5 mixed features with and without DIP symptoms; impact of DSM-5 anxiety features; impact of biological rhythms in mixed depression; impact of impulsivity on mixed depression; and impact of mixed depression in functionality.

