Primary outcome will be change in MADRS from baseline to week 3. Secondary outcomes will be: change in YMRS at the end of week 3 and 6 of treatment; response rates (50% or more of reduction in MADRS at the end of weeks 3 and 6 of treatment); remission rates (MADRS <11 (56) at the end of weeks 3 and 6 of treatment); change in anxious symptoms assessed by Hamilton Anxiety Scale (HAM-A) (57) at the end of weeks 3 and 6 of treatment; change in overall clinical impression assessed by Global Clinical Impression of Severity (GCI-S) (58) and Global Assessment of Functioning (GAF) (59) at the end of weeks 3 and 6 of treatment; change of functionality assessed by abbreviated version of the World Health Organization questionnaire (WHOQOL) (60) at the end of weeks 3 and 6 of treatment; change of biological rhythms assessed by the Biological Rhythm Interview of Assessment in Neuropsychiatry (BRIAN) (61) at the end of weeks 3 and 6 of treatment; change of impulsivity assessed by Barratt Impulsivity Scale (BIS-11) (62) at the end of weeks 3 and 6 of treatment; association between the chronotype assessed by Morningness–Eveningness Questionnaire (63) and the severity of mixed depression assessed by MADRS; and change in neuropsychological battery parameters before and at the end of the intervention (6 weeks).

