### Reasons for Withdrawal or Termination

Patients will be withdrawn from the study if they meet one or more of the following criteria:

(1) Leave the study on their own accord;

(2) Two consecutive visits OR three or more non-consecutive visits;

(3) Have severe clinical or psychiatric events (at clinical assessment) during the study:.

These criteria will be analyzed on a case-by-case basis according to the clinical assessment that the psychiatrist may be considering. Examples of serious clinical events are: neurological deficits, cardiovascular deficits, endocrine decompensation, loss of consciousness, syncope; and others. Examples of serious psychiatric events are: suicidal ideation, suicide attempt, autoaggressiveness (self-mutilation), hetero-agressivity, severe anxiety, severe psychosis, etc.

(4) Serious adverse effects (at clinical assessment) during the study:

These criteria will be analyzed on a case-by-case basis according to the clinical assessment that the psychiatrist may be considering. Examples of serious adverse effects: severe or frequent headaches, severe cervical pain, severe scalp pain, severe scalp burning, severe dizziness, severe nausea, and seizures.

(5) Worsening of depressive (>25% on the MADRS) or manic (>50% on the YMRS) symptomatology at the end of each week of treatment.

Patients with worsening scores on depressive symptom scales (increase on MADRS scores greater than 25%) or manic symptoms (increase on YMRS scores greater than 50%) at the end of each intervention week (compared to the previous week).

Patients who discontinue the study will be referred to the psychiatrist who referred the study for appropriate follow-up and management of the disease.

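### The primary superiority test is run on a per-protocol set judged over six weeks, although the endpoint is at week 3 and the randomised comparison should be primary

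*Protocol article*

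**What the plan says.** All references are to the protocol article.

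- **Hypothesis (Study Hypothesis).** Superiority: active TBS "can produce a greater and statistically significant reduction in the primary outcome scale (MADRS) compared to sham TBS".
- **Endpoint (Measurement of Variables and Outcomes).** "Primary outcome will be change in MADRS from baseline to week 3".
- **Primary analysis set (Statistical Analysis).** "The primary efficacy analysis will be performed using the PP analysis set".
- **PP definition (same section).** Members of the ITT set who "receive the protocol-specified treatment and complete the 6-week treatment regimen or withdrew before completion per the study protocol".
- **ITT definition (same section).** Patients who "met the study eligibility criteria and received at least one week active/sham TBS treatment".
- **Stated use of ITT (same section).** "Comparisons of baseline demographic and clinical characteristics and safety assessments will be performed on the ITT analysis set". A more general sentence says that results will be analysed in both populations, but no efficacy analysis is specifically assigned to ITT.
- **Withdrawal (Reasons for Withdrawal or Termination).** Five criteria: voluntary exit ("Leave the study on their own accord"), a visits criterion, severe clinical or psychiatric events, serious adverse effects, and worsening on MADRS or YMRS. The third and fourth are to be judged case by case.
- **Medication (Inclusion and Exclusion Criteria).** The drug regimen is to stay unchanged until the end of the study.

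**The concern.** In a superiority trial, randomisation protects the comparison only if patients are analysed in the groups to which they were allocated. A set chosen by what patients did after randomisation gives up that protection in the trial's one confirmatory test.

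The timing adds a second difficulty. What happens in weeks 4 to 6 cannot change a week-3 score, but it can decide whether that score is counted. A medication change in week 5, for example, could plausibly follow a poor week-3 result. Excluding such a patient would select on the outcome itself and discard a measurement already made. The article gives no reason for tying a week-3 comparison to later conduct.

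**Working it through.** **1. Timing.** Sessions up to the endpoint: 3 weeks × 5 = 15. Sessions after it: 3 weeks × 2 = 6. The total of 21 agrees with the Discussion. So 6 of the 21 sessions, and a further three weeks of the stable-medication requirement, come after the primary endpoint but fall within the period over which PP is judged.

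**2. Who can be lost from the primary analysis**

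| Patient | In PP? |
|---|---|
| Randomised, then found ineligible | No (outside ITT) |
| Randomised, under one week of TBS | No (outside ITT) |
| Withdraws under a listed criterion | Yes, on the natural reading |
| Withdraws, judged not per protocol | No |
| Week-3 MADRS observed, sessions missed in weeks 4–6 short of withdrawal | Can be excluded as not having received the specified treatment |
| Week-3 MADRS observed, medication changed in weeks 4–6 | Can be excluded on the same ground |

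The withdrawal clause has no firm boundary. If it covers all five criteria, it admits nearly every withdrawal. If it is narrower, someone must decide which withdrawals count, and two of the criteria are themselves case by case.

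**3. Possible size (illustration only).** The article gives no figure for PP exclusions, so the rates below are assumptions: no true effect, 45 per arm (the planned number), outcome SD 1, and exclusion correlated 0.5 with a poor week-3 outcome except in the last row. There were 6,000 simulated trials per row, tested by t-test at two-sided 5%. The nominal 10% is 4 of 45 after rounding; 20% is 9 of 45.

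| Excluded, active vs sham | Bias (SD) | Type I error |
|---|---|---|
| none | 0.00 | 5.0% |
| 10% vs 10% | 0.00 | 5.2% |
| 10% vs 0% | 0.08 | 6.5% |
| 20% vs 10% | 0.09 | 7.6% |
| 20% vs 0% | 0.17 | 12.3% |
| 20% vs 0%, unrelated to outcome | 0.00 | about 5.5% |

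In the same simulations, analysing all 90 gave 4.7% to 5.5% and no bias. Swapping the arms reverses the sign of the bias.

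Check of the 20% vs 0% row by formula:
- Shift = ρ·φ(z)/(1 − p) = 0.5 × 0.280/0.8 = 0.175 SD.
- SE = √(1/36 + 1/45) = 0.224.
- Type I error = P(Z > 1.96 − 0.78) + P(Z < −1.96 − 0.78) ≈ 12%.

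**4. Scale.** The stated 82 patients cannot be rebuilt, because no SD, degrees of freedom or arm size is given for the cited F value; this point does not depend on it. Taking 41 per arm and 90% power at face value, the implied effect is (1.960 + 1.282) × √(2/41) = 0.716 SD. A bias of 0.08 to 0.17 SD is then about 11% to 24% of the planned effect (0.082/0.716 and 0.169/0.716).

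**The case against.** The strongest reply is that PP is wider than its name suggests. A reader who stops at the words "The PP population thus will include all subjects from the ITT set who receive the protocol-specified treatment and complete the 6-week treatment regimen" might infer that PP means 6-week completers, so that sham non-responders and active patients with poor tolerability drop out of the primary test. The documents do not support that. The sentence goes on to admit withdrawals per protocol, and the listed criteria include voluntary exit, adverse effects and worsening. On the natural reading those patients stay in. For the same reason, the 10% dropout in the Sample Size Calculation cannot stand in for the share excluded from PP. This part of the objection stands and narrows the point to the groups in the table under step 2.

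A reader might also infer that the 5% error rate is certainly lost. That is not supported either: it stays near 5% when exclusion is equal in both arms or unrelated to outcome. Participants, operators and raters are blinded to the end of the study, which limits deliberate selection. Blinding does not prevent exclusions related to response or tolerability from differing by arm.

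Finally, the article names two analysis populations, so an ITT efficacy result may be intended. That is arguable, but it would not be the primary result, and this ITT set is not the full randomised set.

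**Conclusion.** The point holds in this limited form. The article fixes the primary efficacy set as per-protocol in a superiority trial, and judges membership over a period that runs three weeks past the endpoint. An analysis plan not shown here would not cure this, because the choice is stated outright.

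Patients with an observed week-3 MADRS can be excluded for deviations in weeks 4 to 6 or for a withdrawal judged not per protocol. Some randomised patients are removed earlier by the ITT definition. The documents do not show that these exclusions will be frequent, related to outcome or unequal between arms, and they contain nothing that rules this out.

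The possible harm therefore runs from almost none to a bias of about 0.17 SD and a type I error of about 12%, in either direction, and only under the assumptions stated. The choice of set needs correcting whatever the size, because it governs the only confirmatory test.

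**What to change.** In the Statistical Analysis section:

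1. Make the primary efficacy analysis all randomised patients, analysed in the arm to which they were randomised, using every MADRS obtained to week 3 in the planned mixed model.
2. Keep PP as a sensitivity analysis of the week-3 endpoint, counting deviations only through week 3.
3. State which withdrawals count as per protocol, by reference to the numbered criteria.
4. Fix PP membership before unblinding.

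The cost is a change of wording, with no extra patients, visits or data. The estimate may differ slightly from the PP one. Power need not suffer: at the implied effect of 0.716 SD, 45 per arm gives Φ(0.716 × √(45/2) − 1.960) = Φ(1.44), about 92.4%, against 90.0% with 41 per arm. That figure ignores missing MADRS values and any dilution of the effect from patients who deviate.

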**Methods:**

The study is designed as a randomized, sham-controlled, double-blinded clinical trial evaluating TBS for the treatment of moderate or severe major depressive episodes with mixed features of patients receiving at least one first or second-line pharmacological treatment for depressive episodes without adequate response. Ninety adult (18 to 65 years old) patients will be enrolled and submitted to 6-week (comprising 5 consecutive days a week sessions for the first 3 weeks and then 2 days a week for a further 3 week) of inhibitory followed by excitatory TBS in dorsolateral prefrontal cortex. Participants will be assessed using clinical and neuropsychological tests before and after the intervention. The primary outcome is change in Montgomery–Åsberg Depression Scale (MADRS) score over time and across groups. Cognitive parameters will also be assessed with neuropsychological tests.

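### The primary mixed model lists no visit or treatment-by-visit term, so on repeated MADRS scores it does not estimate the stated endpoint, change from baseline to week 3

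*Protocol article*

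**What the plan says.** Measurement of Variables and Outcomes fixes the endpoint: "Primary outcome will be change in MADRS from baseline to week 3". Statistical Analysis repeats it and says the arms will be compared "using a linear mixed model (69) with a continuous dependent variable (MADRS score) to measure the primary outcome". It then lists the model terms: "For primary outcome subject will be the random effect and the fixed factors will be intervention (sham × active").

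One further input is mentioned, medication as defined daily dose: "This enables the inclusion of several medications and doses in the model, as medication groups". No section puts visit, treatment-by-visit or baseline MADRS into the model.

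Table 2 schedules MADRS at baseline and at the ends of weeks 1, 2, 3 and 6. The Abstract words the outcome more loosely, as change in MADRS "score over time and across groups".

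**The concern.** A mixed model with a subject random effect is a model for repeated measurements. To give a change by a particular visit it needs terms that let the mean differ by visit and let the arm difference differ by visit. Neither is listed. The named response is the score, not the change, so the one treatment coefficient has to summarise all visits together, including baseline, where treatment cannot yet have acted.

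This is the trial's single primary test. An analyst who follows the text answers a different question from the stated endpoint. An analyst who wants the stated endpoint has to choose the missing terms, possibly after seeing data.

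**Working it through.** **1. The plan's own figure.** Sample Size Calculation gives 82 evaluable patients at 90% power and 5% alpha, citing reductions of 52.5% and 17.4% and F/X² = 6.166, with no SD. Treating the percentages as proportions gives 74 in total (two-sided), or 86 with continuity correction. Reading 6.166 as a two-group F or chi-square gives 34 to 105, depending on the source study's design. So 82 was not reproduced. Without an SD or an explicit effect size this does not show that 82 is wrong, and it does not tie 82 to a week-3 comparison of means. The power figures below therefore start from a hypothetical week-3 comparison with 90% power.

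**2. What the listed model estimates.** With complete data on k visits, a random-intercept model with treatment alone gives

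coefficient = (1/k) × sum over visits of (active mean − sham mean).

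This is algebra and needs no assumed SD or time course. A check on one simulated data set (41 per arm, visits 0 to 3):

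- Fuller model with visit terms: baseline difference −4.82; treatment-by-visit terms +0.70, −4.24 and −3.72 at weeks 1, 2 and 3.
- Arm differences by visit: −4.82, −4.12, −9.06, −8.54. Their mean is −26.54/4 = −6.64.
- The treatment-only model returned −6.64. The week-3 change contrast in the same data was −3.72.

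Here a chance baseline imbalance made the coefficient larger than the endpoint. The error can go in either direction.

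**3. The change-score readings.** With one week-3 change score per patient, treatment alone would estimate the endpoint. But each subject then has one value, so the subject variance and the residual variance cannot be told apart, and the response is no longer the named one. With change scores from several visits, the coefficient is again an average over visits.

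**4. Expected size (assumed time courses).** Let D be the true week-3 difference, with no difference at baseline.

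| Time course | Baseline, weeks 1–3 | With week 6 added |
|---|---|---|
| Linear to week 3, then held | (0 + 1/3 + 2/3 + 1)/4 = 0.50 D | (0 + 1/3 + 2/3 + 1 + 1)/5 = 0.60 D |
| Full from week 1 | (0 + 1 + 1 + 1)/4 = 0.75 D | (0 + 1 + 1 + 1 + 1)/5 = 0.80 D |

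**5. Power (assumed equal SD σ and equal correlation ρ between visits).** The variance of a subject's mean over 4 visits is σ²(1 + 3ρ)/4. Under linear growth the standardised signal is 0.5D / [σ√((1 + 3ρ)/4)] = (D/σ)/√(1 + 3ρ). A week-3 comparison with 90% power has signal 1.960 + 1.282 = 3.242, so power = Φ(3.242/√(1 + 3ρ) − 1.960):

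- ρ = 0.3: Φ(2.352 − 1.960) = 65%
- ρ = 0.5: Φ(2.050 − 1.960) = 54%
- ρ = 0.7: Φ(1.841 − 1.960) = 45%

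If the effect is full from week 1, the signal is 1.5 times as large: Φ(1.5 × 3.242/√(1 + 3ρ) − 1.960) = 94%, 87% and 79%.

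**6. Simulation.** 4,000 trials per scenario, 41 per arm, SD 9, linear growth then held, D = 6.44 points. This D is 0.716 SD, from 3.242 × √(2/41) = 0.716. The treatment-only estimates averaged about −3.2 (weeks 0–3) and −3.9 (with week 6). The week-3 contrasts averaged about −6.4 to −6.5. Power:

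| ρ | Treatment only, weeks 0–3 | Treatment only, with week 6 | Week-3 change, unadjusted | Week 3, adjusted for baseline |
|---|---|---|---|---|
| 0.3 | 0.64 | 0.83 | 0.77 | 0.91 |
| 0.5 | 0.53 | 0.70 | 0.89 | 0.96 |
| 0.7 | 0.44 | 0.59 | 0.99 | over 0.99 |

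At ρ = 0.3 with week 6 included, the treatment-only model has more power than the unadjusted week-3 change contrast, so the loss is not uniform.

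**The case against.** The best defence is that this is a condensed article. Visit coding, covariance structure and covariates are often left to a full protocol or SAP, the text never says the list of fixed factors is complete, and the Abstract's mention of time may show that a time term is intended. That would answer a complaint about missing detail. It does not answer this one: the article chose to name the response, the random effect and the fixed factor, and as named they do not target the endpoint in the preceding sentence.

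Several stronger inferences should be resisted:

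- *Treatment is the only term in the model.* Not so: medication dose is also to be included. It supplies no visit term, so the point stands.
- *The coefficient cannot be the week-3 change under any reading.* With one change score per patient it would be. That reading departs from the named response and leaves the subject random effect without a function.
- *Leaving out baseline MADRS is an error.* If baseline is in the response with visit and treatment-by-visit terms, the week-3 change is estimable without a covariate. Adjustment is a gain in precision.
- *The trial loses its planned 90% power.* The documents do not establish this. They give no SD, correlation or time course, the basis of 82 cannot be recovered, and the loss shrinks or reverses in some of the scenarios above.

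**Conclusion.** The point stands as a mismatch between the stated primary model and the stated primary endpoint. On repeated MADRS scores, the listed model estimates the arm difference averaged over all included visits, baseline among them. That holds whatever the SD or time course. On a single change score, the subject random effect is not identifiable.

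The size is illustrative only. The coefficient targets 50% to 60% of the week-3 difference under linear growth to week 3, and 75% to 80% if the effect is full from week 1. For visits 0 to 3, linear growth and equal correlations, a week-3 comparison with 90% power falls to about 65%, 54% and 45% at correlations 0.3, 0.5 and 0.7. The loss is smaller, and not uniform, once week 6 is included. A reader might conclude that the trial is underpowered or the endpoint ill-defined. The documents support neither: the two Methods sections agree on week 3, and only the Abstract is looser.

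**What to change.** In Statistical Analysis, specify a repeated-measures linear mixed model for MADRS with treatment, categorical visit and treatment-by-visit as fixed effects and correlated within-patient errors. Name the treatment contrast at week 3 as the single primary test. Preferably use the post-baseline visits as response with baseline MADRS as a covariate, since that precision costs nothing. Say how the medication-dose terms enter.

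Correct the next sentence of that section too, which makes the scale scores the random effect for the secondary outcomes; they are the responses. Reword the Abstract's primary outcome to change from baseline to week 3.

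The cost is analysis wording only. All the MADRS data needed are already scheduled, and no visit or sample-size change follows.
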